### Sample Size Determination for Primary End Points

The EPDS scores from baseline to 6 months are used to analyze PPDS in LHMoms and control arms. While we considered PPDS and LE8 as dual primary end points, we chose 1 outcome to base our sample size on, which was PPDSs as defined by an EPDS score >9. This score was specifically chosen because it is used as the screening cutoff to refer for clinical evaluation in our hospital system, as it represents the possible presence of depressive or anxiety symptoms. The rate of EPDS >9 ranges from about 30% to 40% depending on other characteristics of the clinics (we selected 33.5% as the lower tertile of this observed range for our nonintervention group in the power calculation). We project we will observe a reduction in the PPDS proportion from 33.5% in the control arm to 23% in the intervention arm. This yields a minimum detectable difference of 31.5% lower incidence of PPDS in the LHMoms intervention arm compared to the attention control arm at 6 months. Our minimum detectable difference is calculated with a sample size of approximately 450 individuals (225 per study arm), assuming a 1:1 randomization, a design effect of 1.5 to account for variance among sites and doulas, a power of .90, a 2-sided significance level of 0.05, and a 20%-25% attrition. Our recruitment projection is for a sample of 600, 300 per arm; however, we have conservatively built in a 25% attrition rate for the longitudinal study (thus powering from a 450 analytic sample), although in past studies we have achieved 80%-85% retention in studies with a longer 1-year observation period [47-50].

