## Discussion

### Summary and Conclusions

This hybrid type 1 effectiveness- implementation RCT tests a novel nonspecialist intervention to prevent MH and cardiovascular health complications of childbirth. Our design is rigorous—we test the intervention against an attention control and measure numerous secondary outcomes having to do with health care use.

We hypothesize that, compared to attention control participants at 6 months post discharge, intervention arm participants will have at least 31.5% lower incidence of PPDS (score >9 on EPDS), and at least 1-point greater improvement in cardiovascular health using the LE8 score. We also expect that participants randomized to the intervention arm will experience better quality of life, reporting lower perceived stress and substance use and higher rates of resilience and perceived social support. Regarding health care use and satisfaction, we anticipate that more intervention than control individuals will have an indicated health care provider contact within the first 7 days post discharge or attend 6-week postpartum visits. We also hypothesize that intervention participants will report greater patient satisfaction with postpartum care, with higher scores on the CSQ-8 survey than control participants. We have culturally adapted an existing intervention to our local population in NYC, and will also be tracking specifics of implementation that will allow us to adapt the intervention further for other contexts. We will obtain important data from participants and key players in the implementation that will support and inform on the long-term sustainability and scalability of the LHMoms program.

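### For the 6-month comparison of proportions on which the trial is sized, the stated inputs give about 52% power, not 90%, and a 31.5% reduction is not the minimum detectable difference

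*Protocol article*

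**What the plan says.** All the inputs stand in one paragraph of the protocol article, under Sample Size Determination for Primary End Points. Of the two primary end points, the trial is sized on the depressive symptom outcome alone, defined by an EPDS score above 9.

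- Effect: "a reduction in the PPDS proportion from 33.5% in the control arm to 23% in the intervention arm".
- Label given to that effect: "This yields a minimum detectable difference of 31.5% lower incidence of PPDS in the LHMoms intervention arm", compared with attention control at 6 months.
- Sample: "Our minimum detectable difference is calculated with a sample size of approximately 450 individuals (225 per study arm"), "assuming a 1:1 randomization".
- Other inputs: "a design effect of 1.5 to account for variance among sites and doulas, a power of .90, a 2-sided significance level of 0.05".
- Attrition: 600 are to be recruited (300 per arm). With 25% loss this leaves the 450 from which the section says the trial is powered, so attrition has already been taken out of the 225 per arm.

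The Discussion, under Summary and Conclusions, uses the same effect as the trial hypothesis: "at least 31.5% lower incidence of PPDS (score >9 on EPDS").

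**The concern.** Two rates, a sample size per arm, a design effect and a significance level fix the power of a comparison of two proportions. The section states all of these and also states the power, so the claim can be checked without any outside figure. A difference of 10.5 points around a rate near 30%, with 225 per arm before any allowance for clustering, looks too small for 90% power.

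At stake is how the trial is read. If 31.5% is the smallest effect that the trial can detect with 90% power, a non-significant result argues fairly strongly against a benefit of that size. If power for that effect is close to one half, the same result says little. Ethics reviewers, funders and later readers rely on this paragraph to judge which.

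**Working it through.** **Inputs** (all from the sample size section): p1 = 0.335, p2 = 0.23, 225 analysed per arm, 1:1 allocation, design effect 1.5, two-sided alpha 0.05 (z = 1.96), claimed power 0.90 (z = 1.2816).

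**What reproduces.** 600 × 0.75 = 450, or 225 per arm. The relative reduction is 1 − 0.23/0.335 = 31.3%; the printed 31.5% is within rounding of the two rates and is not part of this point.

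**Power with the stated inputs.** Normal approximation for two proportions, with pooled variance under the null:

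- Effective n per arm = 225/1.5 = 150.
- Mean rate = (0.335 + 0.23)/2 = 0.2825.
- SE0 = √(2 × 0.2825 × 0.7175/150) = 0.0520.
- SE1 = √((0.335 × 0.665 + 0.23 × 0.77)/150) = 0.0516.
- Power = Φ((0.105 − 1.96 × SE0)/SE1) = Φ(0.060) = 0.524.

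The choice of formula matters little: unpooled variance gives 0.529, arcsine 0.527 and a continuity correction 0.473.

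**Attempts to reach 0.90** (same pooled formula, 33.5% vs 23%):

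| Reading | n per arm used | Power |
|---|---|---|
| As stated | 150 | 0.524 |
| 20% attrition, design effect kept | 160 | 0.550 |
| No attrition, design effect kept | 200 | 0.646 |
| Design effect ignored | 225 | 0.698 |
| 20% attrition, design effect ignored | 240 | 0.725 |
| No attrition, design effect ignored | 300 | 0.817 |
| As previous row, but one-sided alpha | 300 | 0.889 |
| 225 multiplied by 1.5 instead of divided | 337.5 | 0.859 |

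The row with the design effect ignored also covers the reading in which 225 is already an effective sample size. Power passes 0.90 only if the stated design is abandoned, for example by reading 450 as the number per arm with no design effect (0.939).

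**Control rate.** Over the section's own range of about 30% to 40%, with the same relative reduction and 150 effective per arm, power runs from 0.47 to 0.63.

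**Minimum detectable difference from 33.5%**, found by solving the power formula for p2:

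| n per arm used | Power | p2 | Points | Relative |
|---|---|---|---|---|
| 150 (design effect 1.5) | 0.90 | 17.3% | 16.2 | 48% |
| 150 (design effect 1.5) | 0.80 | 19.3% | 14.2 | 42% |
| 225 (no design effect) | 0.90 | 20.0% | 13.5 | 40% |

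**Size of the gap.** For 33.5% vs 23% at 90% power, n = (1.96 × √(2 × 0.2825 × 0.7175) + 1.2816 × √(0.335 × 0.665 + 0.23 × 0.77))²/0.105² = 384.3, so 385 per arm before clustering. With the design effect this is 385 × 1.5 = 577.5, or 578 analysed per arm, against the 225 planned.

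**The case against.** The strongest reply is that 52% describes a comparison of two proportions at one time point, while the Statistical Analysis section plans linear mixed models on mean EPDS scores. EPDS is collected at baseline and four follow-ups, and a calculation that used this might have relied on a within-person correlation that the article does not print.

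Part of this stands. A reader might infer that the trial as it will be analysed has only about an even chance of detecting its effect. The documents do not support that: power for the mean score depends on a standard deviation and a correlation that they do not give. The 52% belongs to the comparison on which the section sizes the trial.

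The reply does not rescue the 90%. The section bases the sample size on the proportion above the cutoff, expresses the detectable effect as incidence at 6 months, and names no repeated-measures input. Two illustrations, both resting on assumed correlations:

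- For baseline adjustment alone to close the gap, the variance would have to fall by 1 − 150/385 = 61%, a baseline to 6-month correlation of about √0.61 = 0.78.
- If the four follow-ups were averaged, the variance factor is (1 + 3ρ)/4. It must be no more than 150/385 = 0.39, so ρ could be at most about 0.19. At correlations of 0.3 to 0.6, power would be about 0.84 to 0.68. The stated end point is also the 6-month value, not an average.

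A reader might also infer that the hypothesis in the Discussion is wrong. It is not: a hypothesised effect does not become an error because the trial has low power for it, and that sentence does not call 31.5% a minimum detectable difference.

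**Conclusion.** The point holds for the sample size section. For 33.5% vs 23% at 6 months, the stated inputs give about 52% power where 90% is claimed. The design effect is not the whole cause, since leaving it out still gives only about 70%, and all 600 with neither attrition nor clustering about 82%. No use of the stated inputs that was tried reaches 90%. The 31.5% is therefore not the minimum detectable difference at 90% power, which is about 48% relative with the stated design effect.

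This rests on a two-sided, two-proportion normal approximation and on reading the design effect in the usual way, as a divisor of the sample size. It does not rest on any assumed intracluster correlation, and it makes no claim about the power of the planned mixed model.

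**What to change.** In Sample Size Determination for Primary End Points, do one of two things:

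- State that with 450 analysed and a design effect of 1.5, power for 33.5% vs 23% at 6 months is about 52%. Give the minimum detectable difference as 33.5% to about 17.3% at 90% power, or to about 19.3% at 80%.
- If the 90% came from a repeated-measures calculation, name the method and print the correlation and any other input that it needs, so that the figure can be reproduced.

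In either case, call the fall from 33.5% to 23% a projected effect and drop the minimum detectable difference label. The Discussion hypothesis may stay, provided it is not presented as detectable with 90% power.

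The change is to wording only, with no added enrolment and no change to conduct. Its price is a less favourable stated power, about which the ethics board and the funder may ask. The article schedules analysis from September 2029, so the correction can be made before results are seen.

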### Analysis of Secondary End Points

The secondary end points include attendance at obstetric postpartum visits, linkage to primary care, and patient satisfaction (Table 4). The secondary end points are assessed through questionnaires at 3- and 6-month post discharge. The questions assess attendance of obstetric or primary care visits and an EHR review of clinical visits by this study’s team.

Participant satisfaction scores are measured using the CSQ-8 survey administered at 6 months post discharge as part of the long REDCap survey. The CSQ-8 survey consists of 8 questions, each weighing 4 points respectively; the survey consists of a range of responses, with 1 being “this does not apply to me” and 4 being “applies to me” [51]. Scores for the CSQ-8 survey can fall between 8 and 32, with higher scores reflecting greater satisfaction experienced by the participant with the care provided. For the CSQ-8 survey, scores 8-13 indicate poor satisfaction, 14-19 represent fair satisfaction, 20-25 mean good satisfaction, and 26-32 indicate excellent satisfaction. For our study, a 4-point difference on the CSQ-8 survey is defined as “clinically meaningful,” assuming an SD of 6 points [51]. No existing literature or research has a consensus on what point difference on the CSQ-8 survey can be considered “meaningful.” This is likely due to the CSQ-8 survey not being uniform and being applied in various settings. The estimated average for the CSQ-8 score for the control group is 13. This is due to the low satisfaction with care in the population that LHMoms is serving.

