**Figure 3 figure3:**
[figure not shown]
Life’s Essential 8 includes key areas for improving and maintaining cardiovascular health as defined by the American Heart Association.

Quality of life is measured via short (15-minute) and long (30-minute) web-based surveys. Long web-based surveys, administered at baseline, 6 weeks, and 6 months, take 30 minutes to complete and assess psychosocial status and other health behaviors using the EPDS, General Anxiety Disorder Assessment, Pittsburgh Sleep Quality Index, Perceived Stress Scale, Brief Resilience Scale, Scale of Perceived Social Support, Posttraumatic Stress Disorder Checklist for *DSM-5* (*Diagnostic and Statistical Manual of Mental Disorders* [Fifth Edition]), and smoking status. Short web-based surveys, administered at 2 weeks and 3 months post discharge, take 15 minutes to complete and assess psychosocial status using EPDS, General Anxiety Disorder Assessment, and Pittsburgh Sleep Quality Index (Table 3).

**Table 3 table3:** Data are collected via short and long REDCap^a^ surveys, and in-person measurements are taken by this study’s team^b-e^.

Data collection instruments and measures	Long web-based survey, 30-min^b^	Short web-based survey, 15-min^c^	In-person measurements^d^
EPDS^e^	✓	✓	
GAD-7^f^	✓	✓	
AHA^g^ My Life Check (Heart Score)^h^	✓		
PCL-5^i^	✓		
PSS-10^j^	✓		
PSQI^k^	✓	✓	
BRS^l^	✓		
Perceived social support	✓		
Hemoglobin A_1c_^m^			✓
Cholesterol			✓
Weight and height			✓
Blood pressure			✓
Smoking status	✓		

^a^REDCap: Research Electronic Data Capture.

^b^Baseline, 6 weeks, and 6 months.

^c^2 weeks and 3 months.

^d^Baseline, 3 months, and 6 months.

^e^EPDS: Edinburgh Postnatal Depression Scale.

^f^GAD-7: General Anxiety Disorder Assessment.

^g^AHA: American Heart Association.

^h^My Life Check is only completed in baseline and 6–month-long surveys.

^i^PCL-5: Posttraumatic Stress Disorder Checklist for DSM-5 (Diagnostic and Statistical Manual of Mental Disorders [Fifth Edition]).

^j^PSS-10: Perceived Stress Scale.

^k^PSQI: Pittsburgh Sleep Quality Index.

^l^BRS: Brief Resilience Scale.

^m^Hemoglobin A_1c_: glycated hemoglobin.

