In addition to web-based survey administration, study staff collect physiological data at in-person study visits. Staff perform point-of-care testing for total and high-density lipoprotein cholesterol and hemoglobin A_1c_, and measure BP, height, and weight at baseline, 3 months, and 6 months. Point-of-care testing occurs in the hospital shortly after enrollment and at a community location at 3 and 6 months for the convenience of participants.

Health care use is assessed via questions presented to all participants at 3- and 6-month post discharge regarding attendance of obstetric and primary care provider visits. This study’s team also performs an EHR review of clinical visits and encounters to understand contact with the individual health systems. A Client Satisfaction Questionnaire-8 (CSQ-8) is administered at 6 months. All data are collected in a secure REDCap database housed at the main study site. The RCT schema is shown below in Figure 4.

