### Statistical Analysis: Analysis of the Dual Primary End Points

Preliminary statistical analysis examines baseline characteristics between study arms (LHMoms intervention vs attention control) to verify that the randomization generated comparable groups. Categorical variables are summarized as frequencies and proportions. Statistical significance is set at *P*<.05 and tested using chi-square or Fisher Exact tests for variables with low expected frequencies (eg, <5). Continuous variables are described as mean, SD, median, and IQR. Statistical significance is tested using a 2-tailed Student *t* test or Wilcoxon Rank Sum for variables with unequal variance or skewed distributions.

The primary outcome of PPDS is operationalized as the presence or absence of PPD symptoms as indexed by an EPDS score greater than or equal to 9 (EPDS >9) at 6 months post partum (Table 4). Linear mixed models, designed to account for the nonindependence of observations within the same person that is inherent to repeated measures designs, are used to estimate the mean EDPS score with 95% CIs and make group comparisons between the LHMoms intervention and attention control at baseline and 6 months post partum. This approach enables an intention-to-treat analysis whereby all participants randomized into the trial are included in the primary analysis regardless of the number of sessions completed due to the flexibility of linear mixed models to handle the presence of missing data. Baseline characteristics associated with PPDS in univariate regression models (eg, parity) or group imbalance detected at baseline are included in linear mixed models as relevant covariates.

**Table 4 table4:** Primary and secondary outcomes measured in REDCap^a^ surveys assess psychosocial status and other health behaviors, as well as health care use and patient satisfaction.

Primary or secondary	Name of outcome	Specific measure to be used
Primary	PPDS^b^	EPDS^c^≥9
Primary	Cardiovascular health	LE8^d^ (continuous measure)
Secondary	Anxiety	GAD-7^e^
Secondary	Posttraumatic stress disorder	PCL-5^f^
Secondary	Perceived stress	PSS-10^g^
Secondary	Sleep	PSQI^h^
Secondary	Resilience	BRS^i^
Secondary	Social support	Perceived Social Support Scale
Secondary	Health care use	Contact at 7 days; 6 weeks postpartum visit attendance
Secondary	Satisfaction with postpartum care	CSQ-8^j^
Secondary	Implementation process	Focus groups, surveys, and interviews

^a^REDCap: Research Electronic Data Capture.

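### First-week provider contact is first asked about at 3 months, so contacts outside the reviewed health records rest on late self-report; 'indicated' contact also needs reconciling with Table 4

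*Protocol article*

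**What the plan says.** - **Outcome.** Table 4 (Statistical Analysis) defines the secondary outcome of health care use as "Contact at 7 days; 6 weeks postpartum visit attendance". The table caption points to REDCap surveys as the source.
- **Hypothesis.** Summary and Conclusions expects that more intervention than control participants "will have an indicated health care provider contact within the first 7 days post discharge". Table 6 also speaks of an indicated visit. Table 4 has no such restriction.
- **Timing of the questions.** Data Collection: "Health care use is assessed via questions presented to all participants at 3- and 6-month post discharge". Analysis of Secondary End Points repeats it: "The secondary end points are assessed through questionnaires at 3- and 6-month post discharge".
- **Second source.** Data Collection adds that the study "team also performs an EHR review of clinical visits and encounters to understand contact with the individual health systems". Analysis of Secondary End Points also names the record review, right after giving the questionnaire times.
- **Earlier survey.** A short survey goes to both arms at 2 weeks. The scales listed for it are the EPDS, the GAD-7 and the PSQI, with no item on health care use.
- **First week by arm.** Under Participant Groups, intervention doulas call and text daily and look for complications; control participants have no daily doula contact that week. Randomization and Informed Consent states that participants are not blinded.

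**The concern.** An event confined to the first week is first put to participants about 12 weeks after that week ends. Women with a newborn may by then forget a contact or misplace its date. If this happens equally in both arms, the observed difference shrinks. If the arm that had daily calls about complications remembers or dates its contacts better, the difference grows without any true effect. This is the outcome closest to the 7-day emergency detection period, so the trial will want to interpret it.

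The event itself is also described in two ways. Any contact among everyone randomised and indicated contact have different event definitions, and possibly different denominators.

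**Working it through.** The article gives no expected rate, effect size or power for 7-day contact, so there is no stated figure to reproduce.

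**1. Recall interval** (3 months taken as 13 weeks = 91 days)
- Contact on day 0 to 7, asked at day 91: 91 − 7 = 84 to 91 − 0 = 91 days.
- Same contact, asked at day 14: 14 − 7 = 7 to 14 − 0 = 14 days.

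**2. Which contacts are exposed.** A dated record needs no recall and applies to both arms. Data Collection describes the review as showing contact with the individual health systems. Contacts inside those systems are therefore protected; contacts elsewhere are not. The share elsewhere is not given.

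**3. Illustration, all inputs assumed.** Let *p* be the true contact rate, *s* the sensitivity of recall, *c* its specificity (0.95), and *e* the share of true contacts that the EHR review dates, equal in both arms, with self-report deciding the rest.

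Observed rate = p[e + (1 − e)s] + (1 − p)(1 − c)

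*Equal recall in both arms, true difference 10 points:* observed difference = 10 × [e + (1 − e)s − (1 − c)].
- e = 0, s = 0.7: 10 × (0.70 − 0.05) = 6.5 points.
- e = 0, s = 0.8: 10 × (0.80 − 0.05) = 7.5 points.
- e = 0.5, s = 0.7: 10 × (0.50 + 0.35 − 0.05) = 8.0 points.
- e = 0.5, s = 0.8: 10 × (0.50 + 0.40 − 0.05) = 8.5 points.

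*Unequal recall, no true difference:* spurious difference = p(1 − e)(s_int − s_con), with s_int = 0.9 and s_con = 0.8 or 0.7.

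| True rate p | e = 0 | e = 0.5 | e = 1 |
|---|---|---|---|
| 0.30 | 3 to 6 points | 1.5 to 3 | 0 |
| 0.50 | 5 to 10 points | 2.5 to 5 | 0 |
| 0.70 | 7 to 14 points | 3.5 to 7 | 0 |

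With s_int = s_con the spurious difference is 0 at any e. The e = 0 column is the extreme in which the EHR contributes nothing.

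**4. Definitions side by side.** Table 4 counts contact at 7 days with no condition. Summary and Conclusions counts contact that is indicated. The article does not say what makes a contact indicated. If it rested on findings made during week 1, it would be a post-randomisation quantity that the daily calls could influence. If it rested on discharge information, it would not.

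**The case against.** The strongest reply is that the EHR review already answers the problem. It is named in both places that describe the measurement, it dates encounters without recall, and doulas cannot cue it. Participants also deliver at the study hospitals, so much of their care may be recorded there. This stands for contacts inside the reviewed systems. A reader might infer that the 7-day outcome as a whole rests on long recall; the documents do not support that.

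A reader might also infer that the daily calls cue recall in one arm. The article does not say so. It is an inference from unequal doula contact and lack of blinding. More contact in the intervention arm is also the hypothesised effect, so more reporting is not in itself evidence of bias.

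Nor do the documents support the idea that indications are looked for only in the intervention arm. Daily doula scanning is described for that arm alone, but all participants receive a monitor and logbook, controls measure blood pressure daily, and the blood pressure safety protocol under Care and Referrals is not limited to one arm.

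Item wording and source precedence may sit in the full protocol or analysis plan, so their absence from the article is not counted here. The assessment times are different: the article states them twice, and they fit a first-week event poorly. Finally, recruitment began in January 2025, so a change now mixes recall windows. That is a real but small cost.

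**Conclusion.** The point holds in a limited form. Self-report on a first-week outcome is placed 84 to 91 days after the event, although a survey already reaches both arms at 2 weeks. The exposed part is contact outside the reviewed health systems, reported late by unblinded participants. Late recall there can dilute the effect, and recall could differ by arm because first-week doula contact differs. The size is not known from the documents. The figures above rest wholly on assumed recall values, contact rates and EHR coverage; they show direction and scale, not an estimate for this trial.

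Separately, the indicated contact in the hypothesis does not match Table 4, and the two must be reconciled. Both matters concern one secondary outcome. The primary end points and the sample size are untouched. This is a cheap improvement.

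**What to change.** 1. Add one or two items to the 2-week survey in both arms: any provider contact in the first 7 days after discharge, with date and place.
2. Combine these with dated EHR encounters by one written rule, identical in both arms.
3. Analyse any contact within 7 days among all randomised participants, as Table 4 implies.
4. Bring the hypothesis in Summary and Conclusions into line with Table 4. If an indicated-contact version is kept, define the indication from information available at discharge in both arms.
5. Participants already past 2 weeks have only the EHR and the 3-month item. Report the outcome by recall window as a sensitivity check. Start the new item on the same date in both arms, so that 1:1 randomisation within site keeps the window from being confounded with arm.

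Cost: a slightly longer 15-minute survey, a change to a running instrument in the study languages, and two recall windows for one secondary outcome.
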